### Outcome measures

The primary outcome measure of the SPRINT study is the difference in injury proportion between the intervention and the control group in the time period between the registration for the SPRINT study and 1 month after the running event. An RRI is defined as a self-reported injury of the muscles, joints, tendons and/or bones in the lower back or lower extremities (hip, groin, thigh, knee, leg, ankle, foot and toes) that is caused by running (training or competition). The injury has to be severe enough to cause a reduction in running distance, speed, duration or frequency for at least 7 days or three consecutive scheduled training sessions or the injury requires that the runners consults a physician or other health professional.^46^

Secondary outcome measures include the between-group differences in (1) the severity score of running injuries (range 0 to 100), the proportion of substantial overuse injuries (both based on the OSTRC Overuse Injury Questionnaire) and injury proportion of medical attention injuries, (2) injury proportion in runners with previous injuries and (3) RRI locations.

### Statistical analysis

Because the follow-up period of this study is at least 3 months, participants who filled out the baseline questionnaire less than 60 days before the running event will be excluded from the analyses. Descriptive statistics and their corresponding SD and frequency distributions will be calculated for all variables. Consistent with the Consolidated Standards of Reporting Trials statement, intention-to-treat analysis will be performed.^47^ Injury proportions, defined as the percentage of runners who reported a new RRI during follow-up, with 95% CIs will be calculated for all participants and for the intervention and control group separately. The injury proportions of the intervention and control group are compared by calculating the difference with 95% CI. Additionally, ORs with 95% CI will be calculated using univariate logistic regression analysis. Adjusted analysis including potential confounders (eg, age, body mass index and earlier injuries) will be performed using multivariate logistic regression analysis. Subgroup analyses are performed for the following characteristics: previous injuries in the 12 months before the trial, sex, running experience, suffering an RRI at baseline, distance of running event registered for and injury locations. Furthermore, the injury proportion of participants in the intervention group who were compliant with the prevention programme will be compared with the injury proportion of the control group. Participants are regarded as compliant if they indicated in the last follow-up questionnaire that they applied at least one of the advices from the prevention programme to their training sessions. Furthermore, an explorative additional analysis on the number of used steps in relation to the injury risk will be performed. All analyses will be performed in SPPS Statistics 25 and p values <0.05 are regarded as statistically significant.

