### Participants

Potential participants are runners who register for the following running events; DSW Bruggenloop Rotterdam 2019 (15 km), Nacht van Groningen 2020 (10, 16.1 and 21.1 km), NN CPC Loop The Hague 2020 (10 and 21.1 km) and NN Marathon Rotterdam 2020 (10.55 and 42.195 km). On the online registration forms of these running events a question is included, in which the runners are asked whether they are interested in participating in a research project on the prevention of RRIs. Contact information of interested runners is send to the researchers, who will subsequently send more information about the study to these runners. Runners who are still interested in participation are asked to provide electronic informed consent and can immediately fill out the baseline questionnaire.

Only runners aged 18 years or older who register for one of the aforementioned five running events can participate in the SPRINT study. Exclusion criteria include participation in our previous trial on RRI prevention (INSPIRE trial), registration for the running event less than 2 months before the event, no access to internet and/or email and no proper knowledge of the Dutch language. For runners who register for multiple running events, only the first registration is taken into account.

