### Randomisation

After completing the baseline questionnaire, the participants are randomised into either the intervention group or the control group. The randomisation is performed in Microsoft Access with a block size of 40. The randomisation table is generated by an individual from outside the research group and this table is not accessible for the researchers during the inclusion and data collection. Both the participants and the researchers are not blinded for the results of the randomisation.

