#### Step 10: run with joy

### Sample size

Based on our previously conducted RCT, an injury incidence of 38% is expected in recreational runners participating in running events (10 km up to 42.195 km).^11^ The sample size calculation is based on the subgroup analysis on runners with previous injuries. With a risk difference of 5%, a significance level of 0.05 (two-sided testing and a power of 80%), a minimum of 1414 runners with a previous injury in the previous 12 months should be included in the analyses. The sample size is doubled in order to obtain enough power for the primary analyses in the entire study population. Taking a loss to follow-up of 20% into account, a total of 3394 runners (1697 in each group) should be included.

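### The 60-day limit is applied after randomisation instead of before it, so the analysed set is not all randomised runners and the target of 3394 makes no allowance for those dropped

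*Protocol article*

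**What the plan says.** Four statements in the protocol article bear on this point.

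- Participants: the only timing criterion at entry excludes runners for "registration for the running event less than 2 months before the event". The clock is the event registration.
- Randomisation: "After completing the baseline questionnaire, the participants are randomised into either the intervention group or the control group". No check on the date of the questionnaire is described.
- Statistical analysis: "participants who filled out the baseline questionnaire less than 60 days before the running event will be excluded from the analyses". The clock is now the baseline questionnaire. The stated reason is a follow-up of at least 3 months. Two sentences later the section says that "intention-to-treat analysis will be performed".
- Sample size: "Taking a loss to follow-up of 20% into account, a total of 3394 runners (1697 in each group) should be included". Loss to follow-up is the only allowance named.

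**The concern.** The two limits are nearly equal in length but start from different dates. The Participants section describes the steps in between: contact details pass from the event organiser to the researchers, information is sent out, and the runner consents and then completes baseline. Any delay along this route can carry a runner who registered in time past the 60-day mark. Such a runner meets the entry criteria, is allocated to an arm and is later removed.

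Two things are at stake. First, a reader who sees the intention-to-treat statement will take the analysed set to be everyone randomised, apart from those with missing outcomes, and under this rule it is not. Second, the removed runners use up places in the recruitment target if they count towards it. They also complete questionnaires and, in the intervention arm, receive the programme without entering the main comparison. The information needed to screen them out exists before allocation.

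**Working it through.** **Inputs.** From the Sample size section: "an injury incidence of 38% is expected in recreational runners", a risk difference of 5 percentage points (so 33% in the intervention arm if it is a reduction), two-sided 0.05, power 80%, a base number of 1414, doubling, and 20% loss to follow-up. The share of runners removed by the 60-day rule is not given. I assume 2%, 5% and 10% to show the range.

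**Reproducing the plan's figure.** 1414 x 2 = 2828, and 2828 x 1.2 = 3393.6, rounded up to 3394. The doubling and the 20% explain the target completely, so no part of it covers the 60-day rule.

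**Power for the whole population.** With n analysed per arm and unpooled variance,

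power = Phi( 0.05 / sqrt((0.38 x 0.62 + 0.33 x 0.67)/n) - 1.96 ), where 0.38 x 0.62 + 0.33 x 0.67 = 0.2356 + 0.2211 = 0.4567.

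*Starting point, no 60-day exclusions.* 3394 x 0.8 = 2715 analysed, n = 1357.6. The standard error is sqrt(0.4567/1357.6) = 0.01834, 0.05/0.01834 = 2.726, and Phi(0.766) = 77.8%.

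*With a share e removed as well.* Analysed = 3394 x (1 - e) x 0.8, taking the 20% loss to apply equally to those who remain.

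| Assumed share e | Analysed | n per arm | Power | Fall due to the rule |
|---|---|---|---|---|
| 0% | 2715 | 1357.6 | 77.8% | none |
| 2% | 2661 | 1330.4 | 77.0% | 0.8 points |
| 5% | 2579 | 1289.7 | 75.7% | 2.1 points |
| 10% | 2444 | 1221.8 | 73.4% | 4.4 points |

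A pooled-variance calculation agrees within about 0.1 point.

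**What does not belong to this point.** The step from 80% to 77.8% has other causes. At 2828 analysed (1414 per arm) power is 79.4%, because the same formula needs 1434 per arm for 80%. The rest arises because 20% loss was added as 2828 x 1.2 = 3394 rather than 2828/0.8 = 3535. Only the last column of the table can be charged to the 60-day rule.

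**Recruitment needed if the rule stays after randomisation.** To keep 3394 runners who meet the limit, 3394/(1 - e) would have to be randomised: 3464, 3573 or 3772 for 2%, 5% or 10%. If the rule is applied before randomisation, no such addition is needed.

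**The case against.** The strongest reply is that this is a prespecified, objective exclusion with a stated reason, and that the natural reading is intention-to-treat within the population so defined. The baseline date precedes allocation and cannot depend on arm, so the arms remain comparable. This stands. A reader might infer from the words about intention-to-treat that the comparison is biased or that randomisation is broken; the documents do not support that.

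A second reply is that the size is unknown. The two limits are close in length, and runners can fill out baseline as soon as they consent, so very few may be affected. This stands too. A reader might infer that the rule takes power from 80% to the low seventies. That would rest on an assumed share with no source in the protocol, and it would charge the rule with a shortfall that arises elsewhere.

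Third, the protocol does not say outright that runners failing the limit count towards 3394. It says that 3394 should be included, while the base number of 1414 is described as runners included in the analyses. I read 3394 as runners enrolled, because it already contains the allowance for loss. That is a reading, so the shortfall in the analysed number is a possibility and not something the text establishes.

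What survives is more than wording. A later analysis plan could define the analysed set, but it could not prevent these runners from being randomised.

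**Conclusion.** The point holds as a mismatch between the entry rule, the time of randomisation and the analysis exclusion. Under the plan as written, some eligible runners can be randomised and then dropped. The analysed set is then not the one that the intention-to-treat statement implies, and 3394 contains no allowance for them. No bias is expected. The consequence is an avoidable loss of precision of unknown size: about 0.8, 2.1 or 4.4 points of power at assumed shares of 2%, 5% or 10%, measured from 77.8%. These figures rest on 38% versus 33%, on 20% loss among those remaining, and on excluded runners counting towards 3394. The previous-injury subgroup, on which the base number rests ("a minimum of 1414 runners with a previous injury in the previous 12 months should be included in the analyses"), would lose runners as well. The mismatch should be corrected because the correction is almost free, not because the trial's validity is in doubt.

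**What to change.** Make at least 60 days between the baseline questionnaire and the event an eligibility criterion in the Participants section. Check it automatically when baseline is submitted, before allocation. Runners who fail it are not randomised and do not count towards 3394. This keeps the sponsor's own threshold and only moves it. The exclusion sentence in the Statistical analysis section can then go.

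For any runners already randomised inside 60 days:

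- report how many there are in each arm;
- describe the primary set as randomised runners who meet the prespecified 60-day limit;
- add an analysis of all randomised runners as a sensitivity analysis.

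I would not require these late runners in the primary set. Their follow-up is shorter than the stated minimum of 3 months, and some could complete baseline after the first follow-up questionnaire, due 1 month before the event. Including them trades completeness of the randomised set against a shorter period for injuries to occur and for the programme to be used.

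The cost is one date check in the online form, a sentence in each of the two sections, and slightly slower recruitment of countable runners.

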#### Step 1: do not change anything if you have no experience with running injuries

A previous injury is the most important risk factor for a new RRI.^4 14^ Furthermore, the results of the INSPIRE trial showed that the prevention programme seemed to have a negative impact in runners who did not suffer an RRI before.^11^ Therefore, runners without previous RRIs are advised not to change anything in their running behaviour. This is a general advice, that is not further specified to specific parts of running behaviour. Furthermore, all steps of the prevention programme are visible to runners without a history of RRIs. This is to enable them to start using the programme if they do experience pain during running in the future.

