### Measurements

Immediately after providing digital informed consent for the SPRINT study, all participants are asked to fill out the baseline questionnaire. This questionnaire consists of six sections on demographics, training, running events, lifestyle, previous RRIs and health complaints. The items of these sections are described in table 1.

**Table 1 T1:** Items of the baseline questionnaire

Section	Items
Demographics	Sex
	Date of birth
	Height (cm)
	Weight (kg)
Training	Running experience (years)
	Running frequency (times per week)*
	Running time (hours per week)*
	Running distance (km per week)*
	Running speed (min per km)*
	Membership of a running club (yes/no)
	Use of training schedules (yes/no)
	Training surface (paved/unpaved and flat/non-flat)
	Types of training
	Endurance training (%)
	Interval training (%)
	Specific exercises (%)
	Shoe type (neutral/anti-pronation/minimalistic/unknown)
	Number of running shoes
	Advices on running shoes
	Use of bandages (yes/no)
	Use of sport compression socks (yes/no)
	Use of inlays (yes/no)
	Average cadence (steps per min)
	Foot strike pattern (rearfoot/midfoot/forefoot/unknown)
Running events	Previous participation (yes/no)
	Years of participation
	Average participations per year
	Year of last participation
	Distances of previous running events
Lifestyle	Smoking (yes/no)
	Alcohol consumption (average glasses per week)
	SQUASH questionnaire†
Previous running-related injuries	Running-related injury in previous 12 months (yes/no)
	Anatomical location (lower back/buttock/hip/groin/ventral thigh/dorsal thigh/knee/shin/calf/Achilles tendon/ankle/foot/toe)
	Diagnosis
	Onset (sudden/gradually)
	Duration of complaints (weeks)
	Still suffering injury (yes/no)
Health complaints	Presence (yes/no, and if yes, which health complaints)

*Asked for the averages over the last month and last year.

†Short questionnaire to assess health-enhancing physical activity, a validated questionnaire that measures health-enhancing physical activity in large populations.^48 49^

Three follow-up questionnaires are sent to the participants (1 month before, 1 week before and 1 month after the running event). These follow-up questionnaires mainly focus on RRIs (table 2).

**Table 2 T2:** Items of the follow-up questionnaires and injury questionnaire

Questionnaire	Section	Items
Follow-up questionnaire	Running-related injuries	Running injury since filling in previous questionnaire (yes/no)

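### The primary risk difference is valid but unadjusted; standardising it over previous injury would gain modest precision that the planned secondary logistic model cannot give on that scale

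*Protocol article*

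**What the plan says.** All references are to the protocol article.

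- **Outcome measures** sets the scale: "The primary outcome measure of the SPRINT study is the difference in injury proportion between the intervention and the control group".
- **Statistical analysis** gives the main comparison, with no covariates named: "The injury proportions of the intervention and control group are compared by calculating the difference with 95% CI". It continues: "Additionally, ORs with 95% CI will be calculated using univariate logistic regression analysis". Only then comes the adjusted model: "Adjusted analysis including potential confounders (eg, age, body mass index and earlier injuries) will be performed using multivariate logistic regression analysis".
- **Sample size** works on the same scale: a 5-point risk difference from an expected 38%, two-sided 0.05, 80% power.
- **Step 1** of the programme description states: "A previous injury is the most important risk factor for a new RRI".
- **Measurements** says that "all participants are asked to fill out the baseline questionnaire", and Table 1 includes a yes/no item on running injury in the previous 12 months and one on whether the runner is still injured.
- **Randomisation** fixes the order: "After completing the baseline questionnaire, the participants are randomised into either the intervention group or the control group". It mentions blocks of 40 and no stratification factor.

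**The concern.** The runner characteristic that the article ranks highest for prognosis is known for everyone before allocation, yet it plays no part in the estimate on which the trial is sized. It appears in a secondary logistic model, and the reason given is confounding. In a randomised trial, allocation removes confounding in expectation. The statistical reason to adjust for a baseline predictor is precision.

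The planned model cannot deliver that precision where it is wanted. Its treatment coefficient is an odds ratio conditional on the covariates, which differs from the marginal risk difference in both scale and target. The confidence interval for the risk difference stays as wide as if previous injury had never been recorded. At stake is a small amount of power and interval width that could be had from data already collected.

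**Working it through.** **1. The plan's own figure.** Read the assumption as 38% versus 33%. The pooled two-proportion formula per arm is

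n = [1.96·√(2·0.355·0.645) + 0.842·√(0.38·0.62 + 0.33·0.67)]² / 0.05² = 1437.

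The plan's 1414, doubled to 2828, gives 1414 per arm for the whole-population comparison. That is within 2% of 1437 and gives 79.4% power by the same formula. Multiplying, 2828 × 1.2 = 3394, the stated total. So the sizing is reproduced for an unadjusted risk difference, with no gain from covariates built in. (Whether 1414 is adequate for the previously injured subgroup is a separate matter.)

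**2. Variance of the crude difference.** With 1414 per arm:

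SE = √[(0.38·0.62 + 0.33·0.67)/1414] = √(0.4567/1414) = 0.01797.

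The 95% half-width is 1.96 × 0.01797 = 3.52 points, and power is Φ(0.05/0.01797 − 1.96) = 79.5%. (This uses the unpooled SE, hence the 0.1-point difference from step 1.)

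**3. Variance after standardising over previous injury.** Let q be the prevalence of previous injury, and p1 and p0 the risks with and without it in an arm whose overall risk is p. In large samples, p(1−p) in each arm is replaced by

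p(1−p) − q(1−q)(p1−p0)².

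Worked case, q = 50% and OR 2 (both assumed):

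- Control arm: p0 = 0.299, p1 = 0.461, so the term removed is 0.25 × 0.1614² = 0.00651.
- Intervention arm: p0 = 0.254, p1 = 0.406, so the term removed is 0.25 × 0.1512² = 0.00572.
- Reduction: (0.00651 + 0.00572)/0.4567 = 2.7%.
- SE = √(0.4445/1414) = 0.01773, and power is Φ(0.05/0.01773 − 1.96) = 80.5%.

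**4. Range.** The article gives neither q nor the odds ratio, so both are assumed. Prevalences of 30%, 50% and 60% were tried, with previous injury as the only covariate.

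| Assumed OR | Variance cut | SE cut | n per arm needed (crude 1437) | Half-width at 1414 per arm (crude 3.52) | Power at 1414 per arm (crude 79.5%) | Power at 1358 per arm (crude 77.8%) |
|---|---|---|---|---|---|---|
| 1.5 | 0.8-0.9% | 0.4-0.5% | 1424-1426 | 3.51 | 79.8% | 78.2% |
| 2 | 2.4-2.7% | 1.2-1.4% | 1399-1403 | 3.47-3.48 | 80.4-80.5% | 78.8-78.9% |
| 3 | 5.8-6.5% | 3.0-3.3% | 1344-1354 | 3.41-3.42 | 81.8-82.0% | 80.2-80.5% |

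The last column is what remains if exactly 20% of 3394 are lost: 3394 × 0.8 = 2715 in total. Even at an assumed OR of 4 the variance cut does not exceed 10%.

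**5. What the planned logistic model does instead.** At 50% prevalence and 1414 per arm, the crude log odds ratio is −0.219 with SE 0.0787 (|z| = 2.78). Adding previous injury gives −0.225 with SE 0.0798 at OR 2 (|z| = 2.81), or −0.234 with SE 0.0815 at OR 3 (|z| = 2.87). The standard error rises and the coefficient moves away from zero, because the conditional odds ratio is a different quantity. The test becomes slightly stronger, but the interval does not narrow and nothing is returned to the risk difference.

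**The case against.** The strongest reply is that nothing here is wrong. An unadjusted difference in proportions is a valid, unbiased primary analysis of an individually randomised trial. No stratified allocation is stated that would call for adjustment, and outcome, comparison and sample size all use one scale. Earlier injuries are already named as a covariate, and previous injury also defines a subgroup analysis and a secondary outcome. The adjusted logistic test even picks up a little power. The gain at stake is about one power point at OR 2.

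All of that stands, and it limits the point to an efficiency recommendation. It does not remove it: the adjustment is on the wrong scale for the primary estimate, and moving it costs almost nothing.

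Three stronger readings are tempting, and the document does not support them.

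- A reader might infer that the plan leaves open which of the crude difference, crude odds ratio and adjusted odds ratio decides. Outcome measures names the difference as primary, and Statistical analysis introduces the odds ratios as additional, so the order is readable.
- A reader might infer that previous injury is ignored. It is in the plan, in second place.
- A reader might expect a much larger gain from adding current injury, event distance or time to the event. The article gives no strength for any of these as predictors, so no figure can be attached to them. Current injury is also asked within the previous-injury section, so the two items overlap.

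One practical reservation also stands. The plan names SPSS 25, and a standardised difference with a valid interval may need some programming beyond a routine logistic regression.

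**Conclusion.** The point holds as a modest improvement to a valid plan. The primary risk difference is unadjusted, and the planned adjustment sits on the odds-ratio scale, so the predictor that the article ranks first adds nothing to the precision of the estimate the trial is sized on.

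For previous injury alone, with assumed prevalence of 30-60%, variance falls by about 1% (OR 1.5), 2.5% (OR 2) or 6% (OR 3). That is worth about 0.3 to 2.5 power points at 1414 per arm, and nearly the same (0.4 to 2.7) at the 1358 per arm left after 20% loss. These figures rest on a prevalence and an odds ratio that the document does not state, on reading the design as 38% versus 33%, and on large-sample variance. The analysis as planned would not be biased or misleading.

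**What to change.** In Statistical analysis, define the primary estimate as the covariate-standardised (marginal) risk difference with 95% CI. Fit a logistic model with arm and a short list of baseline covariates fixed in advance. Predict each runner's risk under both arms, average the predictions, and take the difference. The list should contain at least running injury in the previous 12 months; current injury at baseline, event distance, age and BMI are reasonable additions. Use an interval that matches the estimator, such as the delta method or the bootstrap. Keep the crude difference and both odds ratios as supportive results. Describe the adjustment as made for precision, not for confounding.

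The primary outcome and its scale do not change. The cost is a few sentences and a little extra programming. The covariates come from the baseline questionnaire and the event registration, so no further data or recruitment are needed.

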		Location (lower back/buttock/hip/groin/ventral thigh/dorsal thigh/knee/shin/calf/Achilles tendon/ankle/foot/toe)
		Onset (sudden/gradually)
		Recurrent injury (yes/no)
		Type (bruise/muscle or tendon injury/sprain/distortion/ ligament injury/ bone fracture/joint dislocation/cartilage or meniscus injury/nerve entrapment/unknown)
		Diagnosis
		Suspected cause
		Severity (OSTRC Overuse Injury Questionnaire*)
		Treatment (yes/no, and if yes, what treatment)
		Use of (pain) medication (yes/no, and if yes, what medication)
		Pain and impairment of activities of daily living-tasks
		Complete recovery (yes/no)
		Duration of complaints (weeks)
	Running behaviour†	RAS questionnaire‡
	Training§	Average running frequency over last month (times per week)
		Average running time over last month (minutes per week)
		Average running distance over last month (km per week)
		Average running speed over last month (minutes per km)
	Injury prevention programme¶	Read programme (yes/no, and if yes, which steps)
		Applied programme to training (yes/no, and if yes, which steps)
Injury questionnaire	Running-related injuries	Date onset injury
		Location (lower back/buttock/hip/groin/ventral thigh/dorsal thigh/knee/shin/calf/Achilles tendon/ankle/foot/toe)
		Pain severity (0–10 Numerical Rating Scale)
		Severity (OSTRC Overuse Injury Questionnaire*)
		Complete recovery (yes/no)

*Oslo Trauma Research Centre Overuse Injury Questionnaire.^50^

†Only included in the first follow-up questionnaire (1 month before the running event).

‡Running Addiction Scale,^51^ translated into Dutch according to the existing guidelines,^52^ included to assess whether specific subgroups of runners are more prone to RRIs due to altered running behaviour are present.

§Only included in the second follow-up questionnaire (1 week before the running event).

¶Only included in the last follow-up questionnaire of the intervention group (1 month after the running event).

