## Discussion

Injuries are a major problem among runners, for which no effective prevention measures have been identified so far. Therefore, the aim of this RCT is to examine the effectiveness of an online injury prevention programme. This programme is aimed at runners who previously suffered from RRIs and includes 10 steps that all deal with one component of running injury prevention. The programme is tested in a large group of runners. Therefore, subgroup analyses based on previous injuries, sex, running experience, distance of running event registered for and injury locations will be possible. Because the programme is presented on a website and mobile application, the programme has the ability to be easily implemented and applied to large and diverse groups of runners if it proves to be effective.

A potential limitation of this study is the use of self-reported RRIs. Runners who are performing with pain may give diverse responses regarding the presence of an RRI. This is partly solved by including the OSTRC Overuse Injury Questionnaire in the follow-up questionnaires, which gives more insight in the severity of the reported RRIs. However, also this questionnaire is patient-reported and subject to the interpretation of the runners. Another possible limitation is that some of the advices in the prevention programme may be subject to the interpretation or motivation of the runners. A runner may, for example, adjust the score on the Numerical

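### Injury location is listed as a subgroup although it is also an outcome, and severity is on its plain reading compared only among runners injured after randomisation

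*Protocol article*

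**What the plan says.** All references are to the protocol article.

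- **Subgroups.** Statistical analysis names previous injury, sex and running experience, and then "suffering an RRI at baseline, distance of running event registered for and injury locations". The Discussion repeats this: "subgroup analyses based on previous injuries, sex, running experience, distance of running event registered for and injury locations will be possible".
- **Location as an outcome.** Outcome measures lists, as items (2) and (3) of the secondary outcomes, "injury proportion in runners with previous injuries and (3) RRI locations".
- **Severity.** Item (1) of the same list is a between-group difference in "the severity score of running injuries (range 0 to 100"), taken from the OSTRC questionnaire. Table 2 under Measurements collects it as "Severity (OSTRC Overuse Injury Questionnaire"), within the block of questions on running-related injuries. No score is assigned to runners who report no injury.
- **Injury proportion.** Statistical analysis gives this a denominator of runners: "defined as the percentage of runners who reported a new RRI during follow-up". It also announces an intention-to-treat analysis.
- **Step 6.** The Discussion concedes that the advice in step 6 to cut back or stop at the first signs of pain may lead a runner to meet the RRI definition, and so may interfere with the primary outcome. It does not consider what this means for severity.

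**The concern.** A subgroup characteristic has to be fixed before treatment can influence it. The location of a new injury is not: it exists only for runners injured during follow-up. Listing it beside sex and running experience contradicts its place among the outcomes, and taken literally it calls for an analysis that cannot be done.

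For severity, the comparison can be done but may mislead. Randomisation balances the arms over all runners, not over those who go on to be injured. If the programme averts mainly mild injuries, those that remain are on average worse, and an effective programme would look harmful on this outcome. If step 6 turns mild pain into countable injuries, the average falls and the programme would look protective without having prevented anything serious. A secondary result on severity is likely to be read together with the primary result, so a wrong sign would matter.

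**Working it through.** The plan gives no figure on this point, so there is none to reproduce. The check uses its injury rates and stated assumptions for the rest.

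**Inputs from the Sample size section:** 38% injured without effect; risk difference of 5 points, hence 33% with the programme; 1414 runners, doubled to 2828 in the analysis, hence 1414 per arm.

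**Assumptions (not in the documents):** mild injuries score 30 and severe ones 60; a share *m* of control injuries is mild, with *m* = 0.5, 0.6 or 0.7; all averted injuries are mild.

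**1. Location as a subgroup.** If *k* runners in an arm have a new injury at a given site, the injury proportion in that subgroup is *k/k* = 100%. This is so in both arms, and the difference is 0 by construction.

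**2. Severity when mild injuries are averted.**
- Control, among injured: 30*m* + 60(1 − *m*)
- Programme, among injured: [30(0.38*m* − 0.05) + 60 × 0.38(1 − *m*)] / 0.33
- Over all runners (uninjured = 0): the control mean times 0.38; the programme mean times 0.33

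For *m* = 0.5, the programme mean among the injured is (30 × 0.14 + 60 × 0.19)/0.33 = 15.6/0.33 = 47.3.

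| *m* | Injured: control | Injured: programme | Difference | All runners: control | All runners: programme | Difference |
|---|---|---|---|---|---|---|
| 0.5 | 45.0 | 47.3 | +2.3 | 17.1 | 15.6 | −1.5 |
| 0.6 | 42.0 | 43.8 | +1.8 | 16.0 | 14.5 | −1.5 |
| 0.7 | 39.0 | 40.4 | +1.4 | 14.8 | 13.3 | −1.5 |

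The signs are opposite. The all-runner difference is 0.05 × 30 = 1.5 in every row.

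**3. Could the wrong sign be significant?** The injured number 0.38 × 1414 ≈ 537 and 0.33 × 1414 ≈ 467. Assume a standard deviation of 10 within each class. With *p* the severe share among the injured, the variance is 30²*p*(1 − *p*) + 10². For *m* = 0.5, *p* is 0.500 (control) and 0.19/0.33 = 0.576 (programme), so the variances are 325 and 319.8. The standard error is √(325/537 + 319.8/467) ≈ 1.14 and *z* = 2.27/1.14 ≈ 2.0. The wrong-direction difference would then be significant about 52% of the time; for *m* = 0.7, about 24%.

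**4. The opposite direction.** If step 6 adds 5 points of mild injuries (38% to 43%, *m* = 0.5), the mean among the injured falls from 45.0 to (30 × 0.24 + 60 × 0.19)/0.43 = 18.6/0.43 = 43.3, with no severe injury prevented. Over all runners it rises from 17.1 to 18.6.

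**5. Averted injuries a random sample of severities.** With *m* = 0.5, mild and severe injuries each fall to 16.5%. The mean among the injured stays at 45.0, while the all-runner mean falls to 0.33 × 45.0 = 14.85. The sign does not reverse, but the injured-only comparison shows none of the benefit.

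**The case against.** **Location.** A reader might infer that the plan certainly conditions on being injured. The text does not establish that. Two other readings involve no post-randomisation selection: the location of the previous injury, which the baseline questionnaire records (Table 1), or location-specific injury proportions over all runners, which fits the protocol's own definition of injury proportion. Because the literal reading gives 100% in both arms, one of these may well be what was intended. This stands. What remains is a contradiction between two sections, repeated in the Discussion, and a term with three possible meanings.

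**Substantial overuse and medical attention injuries.** A reader might place these beside severity as defined on injuries only. Their denominator is not stated in the outcome list, and the general definition of injury proportion counts runners. Naming the denominator is worthwhile, but no error is shown.

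**Size of the severity effect.** The illustration assumes that every averted injury is mild, which is favourable to reversal. The direction can also be the other way, as step 4 of the calculation shows. Reversal is therefore possible, not certain.

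**Severity among the injured as a legitimate description.** This also stands, provided it is labelled as such. Scoring uninjured runners 0 has a price of its own: it partly repeats the primary outcome.

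**Subgroup tests.** A reader might go on to infer that the plan relies on separate tests within subgroups without interaction terms or control of false positives. The article says only that subgroup analyses are performed and gives one general significance threshold. Such detail is commonly left to the full protocol or analysis plan, so no finding is made of it.

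**Conclusion.** The point holds for two items of wording.

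First, injury location cannot be both a subgroup characteristic and an outcome. If new injuries are meant, the subgroup analysis is empty.

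Second, the severity comparison, on its plain reading, is made among runners selected by the primary outcome, and the protocol itself describes a way in which the programme can change that selection. Under the stated assumptions the injured-only mean moves 1.4 to 2.3 points in the wrong direction while the all-runner mean improves by 1.5. With mild injuries added instead, the error runs the other way. The size depends on the assumed scores and on which injuries are averted. There is no such bias if the programme changes neither the number nor the mix of injuries.

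The documents do not support the broader statement that these analyses will reverse the apparent effect, and no reversal is shown for location. The primary comparison of injury proportions is not affected.

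**What to change.** - **Location:** remove it from the subgroup list in Statistical analysis and from the Discussion, or state that the location of the pre-trial injury is meant. Analyse new injury at each location as a yes/no outcome per runner, over all randomised runners.
- **Substantial overuse injury:** define it as yes/no per runner over all randomised runners.
- **Severity:** compare it over all randomised runners, with 0 for those without an RRI, using a rank-based or bootstrap method. Any comparison among injured runners should be labelled descriptive.

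The cost is wording only: no additional data, runners or questionnaires. The drawback is a severity score with many zeros (about 62% to 67% of runners at the planned rates) that partly overlaps with the primary outcome. Keeping the injured-only summary as a description retains the information on how bad the reported injuries were.
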